## Abstract

**Introduction:**

Safety-netting in primary care is the best practice in cancer diagnosis, ensuring that patients are followed up until symptoms are explained or have resolved. Currently, clinicians use haphazard manual solutions. The ubiquitous use of electronic health records provides an opportunity to standardise safety-netting practices.

A new electronic safety-netting toolkit has been introduced to provide systematic ways to track and follow up patients. We will evaluate the effectiveness of this toolkit, which is embedded in a major primary care clinical system in England:Egerton Medical Information System(EMIS)-Web.

**Methods and analysis:**

We will conduct a stepped-wedge cluster RCT in 60 general practices within the RCGP Research and Surveillance Centre (RSC) network. Groups of 10 practices will be randomised into the active phase at 2-monthly intervals over 12 months. All practices will be activated for at least 2 months. The primary outcome is the primary care interval measured as days between the first recorded symptom of cancer (within the year prior to diagnosis) and the subsequent referral to secondary care. Other outcomes include referrals rates and rates of direct access cancer investigation.

Analysis of the clustered stepped-wedge design will model associations using a fixed effect for intervention condition of the cluster at each time step, a fixed effect for time and other covariates, and then include a random effect for practice and for patient to account for correlation between observations from the same centre and from the same participant.

**Ethics and dissemination:**

Ethical approval has been obtained from the North West—Greater Manchester West National Health Service Research Ethics Committee (REC Reference 19/NW/0692). Results will be disseminated in peer-reviewed journals and conferences, and sent to participating practices. They will be published on the University of Oxford Nuffield Department of Primary Care and RCGP RSC websites.

**Trial registration number:**

ISRCTN15913081; Pre-results.

Strengths and limitations of this studyThe safety-netting toolkit being evaluated is already implemented and integrated in the Egerton Medical Information System (EMIS) Web, a brand of electronic health record (EHR), but is rarely used.Data collection will be carried out primarily through existing automated links between the practice EHR and the RCGP Research and Surveillance Centre, surveillance system, thereby limiting the additional research workload for participating practices.We are reliant on the cancer diagnosis, generally made in specialist care, being recorded in the primary care EHR system in a consistent and timely manner.

## Introduction

### Background

Safety-netting is regarded as the ‘best practice’ in cancer diagnosis in primary care.^1^ It aims to ensure patients do not drop through the healthcare net but are followed up until symptoms are explained.^2^ Our research highlights an absence of evidence on how best to safety-net, especially with patients with non-specific cancer symptoms.^1^ Expert consensus, international survey data and interviews with general practitioners (GPs) and patients show that effective patient communication, shared decision making and improved clinical systems are needed to ensure that tests and referrals are followed up and recurrent consultations are identified in patients with unexplained symptoms.^3–5^ To achieve this, significant improvements in electronic health record (EHR) utilisation, particularly data quality, are required, by integrating information and communication technology with clinical care.^6–8^

While there are clear guidance and recommendations for safety netting in primary care,^9^ successful implementation of these recommendations rely on resources available at general practices. Universally accessible National Health Service (NHS) fail safes do not exist to ensure tests are conducted, returned and reconciled.^10^ Confusion exists about which staff member is responsible for test communication.^11^ Patients can be unaware of their responsibility to follow up investigations and referrals, assuming ‘no news is good news,’ and taking no action if they do not feel better or develop new symptoms.^12 13^ The success of a systems-based approach to safety-netting is jeopardised by inadequate administrative processes and marked variation in approaches to follow up.^14^ EHR-based interventions show promise: trials in the USA of electronic prompts increased the proportion of patients with cancer symptoms who receive follow-up.^8 15–17^ However, despite reporting enthusiasm for new initiatives, GPs do not always engage with new information technology, and this driven in part by social and technical factors, such as pop-up fatigue and information overload and being under-resourced.^13 14 18–21^

An electronic safety-netting toolkit (E-SN toolkit) has been developed through consultation with GPs in the UK and was embedded within one of the major clinical systems in England—Egerton Medical Information System (EMIS) Web in May 2018. The toolkit is designed to replace existing verbal or paper methods of safety netting by providing effective means for tracking and follow up by administrative staff. The E-SN toolkit proposes a rigorous, robust, traceable and auditable proactive approach to tracking patients. It is designed to allow clinical data to be entered using templates, and diary entries to be generated (time reminders to check an action has been completed). Using diary entries, users can effectively follow up test requests, referrals and non-specific but concerning symptoms. For instance, outstanding actions appear as ‘Alert Flags’ to identify incomplete diary entries and can be collated. Although the E-SN toolkit is currently available to general practices using EMIS, practices have to proactively turn it on to implement it in their current practice.

This study aims to evaluate the effectiveness of an EHR safety-netting toolkit (E-SN toolkit) for use in primary care with patients with symptoms of cancer.

### Study design

The study will employ a stepped-wedge cluster-randomised controlled trial (SW-CRCT) randomising clusters, that is, general practices, in blocks of 10 to the timing of activation of the E-SN toolkit. General practices will crossover in these blocks to the activated phase every 2 months (figure 1). The study will compare patient’s primary care interval data for cancer diagnoses pre and post E-SN toolkit activation at all participating practices. The stepped-wedge design will ensure that time-related confounders such as seasonal variation should be accounted for.

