Key Secondary Outcomes	Proportion of cancers diagnosed after emergency presentation measured during inactive and active E-SN phases. Recorded new diagnoses in those who have a template activated, measured by cancer site and stage, and by non-cancer diagnosis, during the active E-SN stage. Total time to diagnosis measured from first recorded symptom to definitive diagnosis for all cancer diagnoses during the inactive and active E-SN phases and all diagnoses with template activation during the active E-SN phase No of GP consultations/patient between first record of symptom and cancer referral, measured during the inactive and active E-SN phase Rates of patients completing direct access cancer investigations measured during the inactive and active E-SN phase Rates of patients referred measured as 2-week wait, urgent, and routine, during the inactive and active E-SN phase Timing of template activation within the primary care interval (from first symptom to referral) measured during the active E-SN phase Template activation rate among consulting patients, both total and stratified by individual GP, measured during the active E-SN phase The proportion of diary entries completed measured during the active E-SN phase The reason for template activation measured based on 20 high-level READ codes during the active E-SN phase Symptoms leading to direct access to investigations measured during the active E-SN phase Recorded vague symptoms in the template measured during the active E-SN phase Demographic details of patients with activated templates measured during the active E-SN phase GP type completing template (eg, partner, locum, trainee) measured during the active E-SN phase Diagnostic codes in patients with activated templates measured during the active E-SN phase

EMIS, Egerton Medical Information System; E-SN, electronic safety-netting; GP, general practitioner.

The anticipated length of the study is 18 months. This consists of 3 months recruitment, followed by a 12-month period during which time the intervention will be introduced, and 3 months for analysis.

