## Methods and analyses

### Outcomes and outcome definitions

#### Primary outcome: primary care interval for cancer diagnoses

The primary care interval is defined as the number of days between the first recorded symptoms of cancer (within the year prior to diagnosis) and subsequent referral for secondary cancer care.^22^ In line with published research and guidelines on diagnostic intervals, we will search the patient record for coded symptoms during the year prior to diagnosis for all patients with a cancer diagnosis: 1 year is a trade-off between misattributing unrelated symptoms occurring more than a year before and missing symptoms of relevance by restricting to a shorter period.^22 23^

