### Randomisation and blinding

The eligible practices will be ranked according to their list size from smallest to the largest by the RCGP RSC. These will then be stratified into 10 strata (by list size) such that each strata contains the same number of practices. This is based on the allocation of 10 practices per step. Practices will be randomised in blocks of 10 to the timing of activation of the E-SN toolkit and will crossover in these blocks to the activated phase every 2 months. Therefore, practices will contribute between 2 months and 12 months of E-SN toolkit-activated time (figure 1).

A statistician ([name], Nuffield Department of Primary Care Health Sciences, University of Oxford) who is independent to the intervention development and implementation will produce a stratified randomisation schedule so that within each strata, practices are randomly allocated to each of the six steps, with some replacement practices. The random sequence will be generated using R software. The allocation will be undertaken for all practices at the same time. Where replacement practices are required, these will be taken from the same strata where possible. If no replacement practices from the same strata are available a coin toss will determine whether the next highest or lowest strata will be used to provide replacement practices.

Given the practice change nature of the intervention, clinicians and practice managers will be aware when their practice has switched to the intervention period. Consulting patients providing outcome data will not be informed of the experimental nature of the E-SN toolkit activation and therefore will be blind to the stage of study occurring in the practice they attended. Study personnel involved in extracting outcome data will be blind to the allocated order of the delivery of the intervention across the practices. All data management of extracted data to calculate the outcome measures will be conducted blinded to the timing of switching to intervention. Similar methods have been used in other implementation SW-CRCTs.^26^

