### Data extraction

Data extractions from all participating practices will correspond to two major time points: at the start of the introduction to the stepped wedge implementation of the E-SN toolkit, and at the end of the stepped wedge period (12 months later). At these two time points, consultation data from the participating practices will be obtained for the previous 24 months. Data from the previous 24 months are required to identify cancers detected in 12 months prior to start, plus the first recorded symptom of cancer during the primary care interval, allowing for this interval to cover up to a year prior to diagnosis.

Records from all patients who are adults aged 18 years and above, registered at participating practices and who have not opted out of sharing data for research purposes will be extracted. Pseudonymised patient information will include: demographic information of age, sex, dates of clinical consultations; coded consultation data for symptoms, diagnoses, tests ordered and referrals made within the consultation records. Where a definitive diagnosis has been made (for cancer and non-cancer conditions), the clinical features recorded in the year prior to diagnosis will be captured. These actions will be achieved by extraction of the EHR rather than by hand searching notes.

Practices will be asked to search for open diary entries every week during the intervention period, and to download and save these to an Excel spreadsheet (locally). The central study research team will use these spreadsheets to track which diary entries are closed during the course of the intervention.

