### Statistical analysis

In patients with a diagnosis of cancer, we will calculate the primary outcome of primary care interval (time between first recorded symptom and referral), proportion diagnosed after emergency presentation and the recorded diagnosis. Among consulting patients, we will calculate the rate of direct access cancer investigation and rates of referrals via 2 weeks wait, urgent and routine pathways, as well as the number of consultations during the primary care interval, and the template activation rate. A patient referred to: a 2-week wait pathway will be reviewed by a specialist within 2 weeks; an urgent pathway will be reviewed as a priority but the exact timing varies between specialty and healthcare setting; a routine pathway requires specialist review but on a non-urgent basis.

Regarding the analysis of the stepped-wedge design and the effect of correlation of observations within clusters, will model the association using a fixed effect for the intervention condition of the cluster at each time step, a fixed effect for time and other covariates (eg, changes in cancer guidelines), and then include a random effect for practice and a random effect for patient to account for correlation of the observations from the same centre and from the same participant.

Analyses will include all patients registered at participating practices. Practices that withdraw their agreement to participate will be included in analyses up to the point of withdrawal, unless they indicate that they wish to withdraw previously collected data from analysis.

Our primary analysis will be carried out on an intention to treat principle. Therefore, if any practice does not switch on the E-SN toolkit at the correct time for their cluster, we will carry out the analysis under the assumption that the E-SN toolkit was switched on at the correct time.

The primary care interval is defined from the presence of symptoms and referral in the primary care record. Symptoms of interest will include all symptoms included in the urgent referral guidelines including vague symptoms such as weight loss, tiredness and back pain.^35 36^ Missing data for these variables in the record will be interpreted as the absence of symptoms or referral, respectively. Extracted data from the primary care record will be limited to the study period plus the preceding year, so symptoms recorded prior to this will not be visible to the research team.

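### Cancers appear to be placed before or after activation by diagnosis date, but the primary interval ends at referral; intervals finished before activation would then count as exposed and dilute the effect

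*Protocol article*

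**What the plan says.** - **Outcome.** The primary care interval runs from the first recorded symptom, within the year before diagnosis, to "subsequent referral for secondary cancer care" (Primary outcome section; Table 2).
- **Comparison.** Study design says the trial will compare patients' "primary care interval data for cancer diagnoses pre and post E-SN toolkit activation".
- **Extraction.** Data extraction asks for 24 months of records in order to "identify cancers detected in 12 months prior to start, plus the first recorded symptom of cancer during the primary care interval". The window is set by when the cancer was detected, with a look-back for symptoms.
- **Sample size.** The 8–9 cancers per cluster per 2-month step come from the annual rate of new cancers (53 per practice).
- **Model.** Statistical analysis uses "a fixed effect for the intervention condition of the cluster at each time step", plus fixed time effects and random effects for practice and patient. It mentions no transition period.
- **Active time.** Under Randomisation and blinding, "practices will contribute between 2 months and 12 months of E-SN toolkit-activated time".
- **Wording that points elsewhere.** Table 1 registers the primary outcome as the interval measured during the inactive and active phases, which does not tie the phase to diagnosis. Table 1 also has "all cancer diagnoses during the inactive and active E-SN phases", but this belongs to total time to diagnosis, a secondary outcome that does end at diagnosis.

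**The concern.** On the non-emergency routes, referral comes before diagnosis. A cancer referred shortly before activation and diagnosed shortly after it has an interval that was already closed when the toolkit was switched on. Dating by diagnosis puts that interval in the active phase. The error goes one way: unexposed intervals are counted as exposed, so the estimate shrinks towards zero.

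The affected cancers cluster in the first months after activation. A stepped-wedge estimate draws much of its information from those months, and they are the whole active period of the last block. A null result could then mean either an ineffective toolkit or misdated exposure.

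**Working it through.** **Inputs from the article:** 60 practices in six blocks of 10; 2-month steps; a 12-month pre-period (taken as six 2-month periods); 9 cancers per practice per step; range 0–60 days and a minimum detectable difference of 2 days at 80% power (Sample size, Table 3).

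**Assumed, because not given:** two-sided alpha 0.05; SD 15 days (range 60 / 4); intracluster correlation (ICC) 0 to 0.05; referral-to-diagnosis time *d* of 14, 30 or 60 days, either fixed or exponential with that mean. The only related figure is specialist review within 2 weeks on the fastest pathway.

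**Step 1: reproduce the article's figure.** The model is generalised least squares with fixed period effects and a random practice effect, and MDD = (1.96 + 0.84) × SE. With SE 0.655 (ICC 0) to 0.719 (ICC 0.05), MDD = 1.83 to 2.01 days. This agrees with the stated 2 days, although the match depends on the assumed SD and ICC.

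**Step 2: weight by time since activation.** The same estimator gives these weights to the first to sixth active step:
- ICC 0: 0.43, 0.29, 0.17, 0.09, 0.03, 0.00
- ICC 0.05: 0.54, 0.32, 0.16, 0.04, −0.03, −0.04

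The first 2 active months carry about half of the estimate.

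**Step 3: share referred before activation.** A step lasts 365/6 = 60.8 days. For a fixed delay, the share in the first active step is d/60.8:
- 14/60.8 = 0.23
- 30/60.8 = 0.49
- 60/60.8 = 0.99

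For an exponential delay it is (d/60.8) × (1 − e^(−60.8/d)), giving 0.23, 0.43 and 0.63, with a small tail in later steps. Over all active time (mean 7 months) the share is 6.6%, 14% and 26–28%.

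**Step 4: effect retained and power.** Retained fraction a = sum over active steps of weight × (1 − share). Fixed delay examples:
- 14 days: 1 − 0.43 × 0.23 = 0.90 (ICC 0); 1 − 0.54 × 0.23 = 0.88 (ICC 0.05)
- 30 days: 1 − 0.43 × 0.49 = 0.79 (ICC 0); 0.73 (ICC 0.05, unrounded inputs)

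Power at the MDD = Φ(2.80a − 1.96).

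| Assumed delay | Effect retained | Power (80% planned) |
|---|---|---|
| 14 days | 0.88–0.90 | 69–71% |
| 30 days | 0.73–0.80 | 54–61% |
| 60 days | 0.46–0.65 | 25–44% |

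Ranges cover ICC 0–0.05 and both delay shapes.

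**Step 5: emergency presentations.** Table 2 defines these as diagnosed before referral, and Sample size puts them at about 19%. If they are counted as correctly classified, the retained fraction is 0.81a + 0.19, which at 30 days gives 0.78–0.84.

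**Step 6: what referral dating leaves behind.** Some intervals start before activation and end after it. Take the all-cancer quartiles in Sample size (0, 5 and 27 days) and the 90th centile of 60, interpolate linearly and cap at 60. The mean capped interval is 0.25 × 0 + 0.25 × 2.5 + 0.25 × 16 + 0.15 × 43.5 + 0.10 × 60 = 17.15 days. Then 17.15/60.8 = 28% of referrals in the first active step would have a first symptom before activation. These intervals are only partly exposed and are not in the table above.

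**The case against.** **The article never states the index date.** This is correct. In the Study design sentence, the reference to cancer diagnoses could simply name the population. The extraction sentence explains why 24 months are needed. The count per step would be about the same by referral date. The registered primary outcome dates the interval, not the diagnosis. A derivation rule may also sit in the full protocol or the analysis plan. What remains is that wherever the article does attach a date to a cancer, that date is diagnosis, and following this wording produces the dilution.

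**The size rests on an assumed delay.** This also stands, and it is why a range is shown. Fourteen days is a modest choice, since even the fastest pathway allows 2 weeks to specialist review.

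**Referral is the event the toolkit aims to bring forward.** True, but the toolkit acts only from activation, so it cannot move a referral from after activation to before it. The inactive or active label is therefore safe; only the calendar step may shift.

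**Stronger readings that the article does not support:**
- A reader might infer that diagnosis dating is fixed as the rule. It is not.
- A reader might infer that any cancer diagnosed within days of activation was referred before it. Emergency cases are not.
- A reader might infer from the condition term that a full, constant effect from the first day is assumed. The article does not say so, and training comes before the switch.
- A reader might expect referral dating to remove the problem entirely. Straddling intervals remain.

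**Conclusion.** The concern holds conditionally and should be fixed before analysis. If phase follows diagnosis date, as the wording suggests, the primary estimate is biased towards no effect, because the outcome closes at referral. A true 2-day effect would be estimated at about 1.8 days for a 14-day delay (2 × 0.88 to 2 × 0.90), 1.5–1.6 days for 30 days and 0.9–1.3 days for 60 days, somewhat less diluted if emergency presentations are counted as correctly classified.

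The direction follows from the article's definitions. The size depends on the unstated referral-to-diagnosis time, and the power figures also on the assumed ICC. If referral dating was always intended, one sentence settles the matter.

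**What to change.** - State that each cancer in the primary analysis is assigned to a step and condition by its referral date, so that an interval completed before activation counts as inactive.
- Keep assignment by diagnosis date as a sensitivity analysis.
- Add a sensitivity analysis excluding intervals that straddle activation. Read it beside the main result and not in its place: it removes mainly long intervals from the active side, which by itself makes that side look shorter.

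**Cost.** This is a derivation rule. Referrals and consultation dates are already in the planned extraction, so neither design nor data collection changes. The downside is that some patients referred late in the study will not yet be diagnosed at the last extraction. This loss may differ by condition, since the toolkit also tracks referrals and tests. It can be checked by repeating the analysis without the final step. All practices are active then, so that step adds little: dropping it raises the SE by about 1% or less (ICC 0–0.05).
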